### Economic evaluation

To compare relative costs and outcomes of the study conditions, we will conduct cost-effectiveness and cost-utility analyses from the perspectives of employers and the society. In both analyses, the incremental cost-effectiveness ratio (ICER) will be calculated for a 6-months period using the following formula: ICER = (Cost intervention group-Cost control group)/(Effect intervention group-effect control group) [82]. Treatment response will be the outcome to estimate the cost-effectiveness of the intervention whereas quality-adjusted life years (QALYs) will be the outcome to estimate cost-utility. The incremental cumulative costs will be calculated as the differences in the costs between the intervention groups and the control group. Costs to be estimated consist of direct costs for developing and maintaining the intervention, costs for staffing (i.e., for providing feedback and technical support), and opportunity costs caused by time spending on the intervention. The non-parametric bootstrap method will be used to handle uncertainty in the ICER. In addition, results will be shown in a cost-effectiveness acceptability curve [83].

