### Measures

#### Primary outcome

Primary outcome will be the self-reported alcohol consumption (standard units) during the 7 days prior to T2, using the Timeline Followback (TLFB) method [52]. The TLFB has been shown to be a valid and reliable procedure to document recent drinking histories [53]. The procedure has been proven to capture drinking levels very well compared to a daily diary [54]. It has been also validated as a web-based version [55]. Respondents retrospectively record their daily drinking by choosing the amount and kind of drinks they had out of a set of typical alcoholic drinks (e.g. a 330 ml bottle of beer or a 100 ml glass of wine). These quantities will be automatically converted to alcohol standard units and added to calculate the total sum score of units for the last 7 days.

As a secondary drinking measure, participants will be coded as responders if their drinking remains within the margin of low-risk, i.e., drinking not more than 14 (women) or 21 (men) standard units per week. Besides the drinking level, several other variables will be assessed as secondary outcomes (Table 2).

**Table 2 Tab2:** Secondary outcome measures and assessment points

Outcome measures	T1	T2	T3
Alcoholic Drinks (Timeline Followback method)	✓	✓	✓
Alcohol Problems Questionnaire (APQ)	✓		✓
Readiness to Change Questionnaire (RTCQ)	✓	✓	✓
Depression Anxiety Stress Scale (DASS-21)	✓	✓	✓
Irritation Scale (IS)	✓	✓	✓
Effort Reward Imbalance Questionnaire (ERI-SF)	✓		✓
Work Limitations Questionnaire (WLQ)	✓	✓	✓
Single-Item Presenteeism Question	✓	✓	✓
Single item question on work ability	✓	✓	✓
General Self-Efficacy Scale (GSE)	✓	✓	✓
Assessment of Quality of Life (AQoL-8D)	✓	✓	✓
Trimbos and institute of Medical Technology Assessment Cost Questionnaire for Psychiatry (TiC–P-G)	✓		✓
Attitudes toward seeking psychological help (ATSPPH-SF)	✓	✓	✓
Use of other health services		✓	✓
Negative-Effects of Psychotherapy Inventory (INEP)			✓
Client Satisfaction Questionnaire (CSQ-8)		✓	

T1 = baseline assessment before randomization, T2 = post assessment after 6 weeks, T3 = follow-up assessment after 6 months

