##### Cost measure

A German version of the Trimbos and Institute of Medical Technology Assessment Cost Questionnaire for Psychiatry (TiC–P-G) [78] will be used to record direct and indirect medical costs over the previous three months. Direct costs can be derived from information on the participants’ use of health services (e.g. general practice visits, sessions with psychiatrists, hospital days). To assess indirect costs participants register the number of “work loss” days (absenteeism from work) and the number of “work cut-back” days, i.e., days on that they were showing up for work despite of feeling ill (presenteeism). The questionnaire shows a good retest-reliability and achieves comparable results between patient-reported data and data derived from medical registrations [78].

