### Clinical evaluation

Analyses of covariance with baseline scores as covariate will be conducted to explore the effects of the interventions compared to the control group on all primary and secondary outcomes. A-priori contrasts will be defined to test the separate effects of the guided and unguided interventions compared to the control condition. For all analyses, Cohen’s d will be calculated by subtracting the average change scores from baseline to post-assessment (T1-T2) of one study group from the other one and then dividing it by the pooled standard deviations of the change scores. We will also calculate the number needed to treat (NNT) with adherence-focused guided and unguided CWT to achieve one response, i.e., complying with the low-risk guideline, compared to the control group. For all statistical analyses, significance level will be set at p < .05 for two-sided tests.

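### The economic evaluation does not carry baseline adjustment into the QALYs and costs of the ICER, which costs precision and lets chance imbalance move the realised ratio

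*Protocol article*

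**What the plan says.** All references are to the protocol article.

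- **Economic evaluation.** The ICER over 6 months is the between-group difference in cost divided by the between-group difference in effect. For costs: "The incremental cumulative costs will be calculated as the differences in the costs between the intervention groups and the control group". Treatment response is the effect in the cost-effectiveness analysis. In the other analysis, "quality-adjusted life years (QALYs) will be the outcome to estimate cost-utility". On uncertainty: "The non-parametric bootstrap method will be used to handle uncertainty in the ICER". An acceptability curve follows. No covariate is named.
- **Clinical evaluation.** "Analyses of covariance with baseline scores as covariate will be conducted to explore the effects of the interventions compared to the control group". The sentence goes on to cover every primary and secondary outcome.
- **Table 2 (under Primary outcome).** AQoL-8D is listed at T1, T2 and T3, and TiC-P-G at T1 and T3, both as secondary outcome measures. Study design places T1 before allocation.
- **Cost measure.** The TiC-P-G "will be used to record direct and indirect medical costs over the previous three months".

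**The concern.** Two adjacent sections describe the between-group comparison differently. The clinical one conditions on the baseline score. The economic one takes group differences and goes straight to the bootstrap. The natural reading is that the increments in the ICER are not baseline-adjusted.

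That matters most for QALYs. If they are computed as an area under the utility curve, T1 utility is one of the points on the curve and also predicts the later points. Health-care use and work loss before randomisation likewise predict later costs, though usually less strongly. Without adjustment, a chance difference in either at T1 passes partly into the numerator or denominator of the ICER, and variance that T1 could explain stays in the interval and the acceptability curve. The economic question is one of the three numbered aims and has its own hypothesis.

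**Working it through.** **1. Arm size.** The plan gives 528 participants in three equal arms, d = 0.30, 80% power and two-sided alpha 0.05. The normal approximation gives 2 × (1.960 + 0.842)² / 0.30² = 174.4, so 175 per arm. The t-test calculation gives 175.4, so 176 per arm and 3 × 176 = 528 (power 0.801). The stated figure reproduces, and n = 176 is used below.

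**2. Size of a chance baseline imbalance.** The standard error of the T1 difference between two arms is SD × √(2/176) = 0.107 SD. A difference above 0.1 SD in either direction has probability 35%, and above 0.2 SD 6%.

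**3. QALY model (assumed).** The article gives no QALY formula, utility SD or correlation. I take the trapezoid area over weeks 0, 6 and 26, equal SD at each visit and a common inter-visit correlation r. The weights in years are 3/52, 13/52 and 10/52, that is 0.0577, 0.2500 and 0.1923 (sum 0.5). In units of the utility SD:

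- variance of the QALY: v = (1 − r) × 0.1028 + r × 0.25, where 0.1028 is the sum of squared weights;
- slope of the QALY on T1 utility: c = 0.0577 + 0.4423 r;
- ratio of adjusted to raw standard error: √(1 − c²/v).

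The shift from a one-standard-error imbalance is c × 0.1066 × SD.

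| r | v | c | SE ratio | Variance saved | Shift, SD 0.15 | Shift, SD 0.25 |
|---|---|---|---|---|---|---|
| 0.3 | 0.147 | 0.190 | 0.87 | 25% | 0.0030 | 0.0051 |
| 0.5 | 0.176 | 0.279 | 0.75 | 44% | 0.0045 | 0.0074 |
| 0.7 | 0.206 | 0.367 | 0.59 | 66% | 0.0059 | 0.0098 |

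For scale, the raw standard error of the QALY difference is √v × 0.1066 × SD. That is 0.0061 at r = 0.3 and SD 0.15, and 0.0121 at r = 0.7 and SD 0.25. The adjusted values are 0.0053 and 0.0071.

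Of the slope c, only 0.0577 comes from T1 being a point on the curve. The rest is prediction of later utility.

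**4. Costs (correlation assumed).** With correlation ρ between T1 and follow-up TiC-P-G costs, the standard error ratio is √(1 − ρ²): 0.98 at ρ = 0.2, 0.92 at 0.4 and 0.80 at 0.6. A 0.1 SD imbalance moves the cost difference by 0.02 to 0.06 SD across ρ = 0.2 to 0.6, against a raw standard error of 0.107 SD.

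**The case against.** The strongest reply is that the section never says the differences are raw. The formula is the generic definition of an ICER and a regression-adjusted difference fits it equally well. The sentence on increments concerns costs only, there is no calculation rule for QALYs, and a journal article may leave estimation detail to an analysis plan that is not shown. This stands in part: a reader might infer that the plan prescribes unadjusted estimation, and the text does not go that far. What remains is that the section says how the increments will be calculated and does not take up the adjustment described just before it.

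Three other readings are tempting and are not supported.

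- **That the T1 measurements go unused.** The ANCOVA covers all secondary outcomes, and Table 2 lists both instruments among them. A QALY would also normally include T1 utility. The gap concerns only the derived QALYs and cumulative costs in the ICER.
- **That the ICER is biased or the bootstrap invalid.** Allocation is randomised, so the unadjusted differences are unbiased in expectation, and resampling reflects the variability due to imbalance. The interval is wider than it need be and is centred on the unadjusted estimate, but it is not wrong.
- **That ordinary imbalance would equal or reverse the QALY effect.** Carrying a one-standard-error imbalance in full through half a year gives 0.1066 × SD × 0.5 = 0.008 to 0.013 QALY for SD 0.15 to 0.25, but that requires r = 1. The article also states no expected QALY difference to compare it with.

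The scope has limits too. The response-based effect term does not depend on AQoL-8D, and the intervention costs (development, staffing, participant time) have no T1 counterpart.

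**Conclusion.** The point holds as one of efficiency and robustness, not of validity. As written, the economic section does not extend baseline adjustment to the QALYs and costs in the ICER, although suitable covariates are measured before allocation.

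For QALYs the gain from adjusting is clear throughout the range examined, with the smallest reduction in standard error about 13% (r = 0.3). For costs it runs from negligible to moderate. Every SD and correlation used is an assumption, since the article reports none. The standard error ratios do not depend on the arm size. The QALY shifts do, and would be larger if fewer than 176 per arm contribute data.

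**What to change.** Add to the Economic evaluation section that, within each bootstrap replicate:

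1. incremental QALYs are estimated by regression on arm and T1 AQoL-8D utility;
2. incremental TiC-P-G-based costs are estimated by regression on arm and T1 TiC-P-G costs, with both models fitted to the same resample so that the cost-effect correlation is kept;
3. intervention costs, which have no baseline value, are added to give total incremental cost;
4. the ICER and the acceptability curve are formed from these adjusted differences.

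The T1 cost covariate can serve as it stands. It covers the three months before T1, and a covariate need not span the same period as the outcome. The response-based effect term needs no AQoL-8D adjustment. If a full analysis plan already adjusts in this way, one sentence saying so is enough.

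The cost is a few lines of text and analysis code. No extra data, visits or participants are needed.

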### Ethical considerations

This study has been approved by the ethics committee of the Leuphana University of Lueneburg, Germany (No. [name]201404_OT).

## Discussion

Problematic alcohol consumption among the workforce is a high-risk factor for individuals in terms of disease burden, and it can lead to high costs for employers and society [1, 2, 8]. As a low-threshold health program, web-based interventions can help people displaying problematic drinking behavior [29]. However, the effects of interventions for reducing alcohol consumption are, on average, small [28, 29, 79]. While there have been a few studies on the efficacy of these kinds of interventions in the workforce [30–32], to the best of our knowledge, no research has been done on cost-effectiveness.

Based on a sample of employees from different sectors, this study provides further evidence for the (cost-)effectiveness of web-based interventions for reducing problematic alcohol consumption in the workforce. The CWT intervention draws on components of traditional methods to treat alcoholism, such as self-monitoring and reflecting on drinking behavior. In addition, techniques commonly used in cognitive-behavioral therapy and emotion regulation trainings are integral elements of the training. To the best of our knowledge, there has been no web-based intervention for reducing problematic alcohol consumption that has integrated emotional psychoeducation and emotion regulation techniques. Given that recent research provide evidence for the relevance of emotion regulation skills for abstinence from alcohol [50], integrating these techniques in interventions for problematic alcohol use may be a promising strategy to further increase the effectiveness of such interventions.

Although there are hints that guided interventions are superior compared to unguided interventions in different health problem domains [34, 84, 85], it is unclear whether this holds for interventions for reducing problematic alcohol consumption. There may be only one study directly comparing different types of guidance in a web-based intervention within the same trial [86], but there is no study on the workforce. Research on the cost-effectiveness of these interventions is also scarce. Because the operational costs of these interventions may particularly be related to the level of guidance, it is of major interest to both employers and health care providers which type of intervention is more cost-effective. The more people use an unguided intervention, the lower the costs [87]. In contrast, the costs for personnel in guided interventions are fixed and will not decrease when the number of users rises. In this three-armed trial, it will be possible to explore both the clinical effectiveness and cost-effectiveness of guided and unguided interventions.

This study has the following limitations: First, we chose a recruiting strategy that is based on the occupational health programs of several health insurance companies and did not focus on specific industrial sectors (e.g. finance, social services, health care, manufacturing, retail, or government) or specific occupational groups (e.g. managers or blue-collar workers). On the one hand, this allows us to estimate the mean (cost)-effectiveness of the intervention for the workforce. On the other hand, this certainly reduces the internal validity of the study because we cannot determine the (cost)-effectiveness for specific industrial sectors or occupational groups. Moreover, employees need to apply actively for study participation. Hence, the results may not generalize to non-help-seeking populations. Second, the economic evaluation to be conducted in this study will be based on actual intervention costs (direct intervention costs + opportunity costs for the participants). Costs associated with the implementation of the intervention (e.g. marketing) will not be considered. Third, attrition is often a problem in web-based interventions [88, 89]. Although we developed the intervention in a way that we hope keeps participants on track (e.g. they engage with integrated multimedia tools, keep an online-diary, and learn about individuals who successfully navigated exemplary situations), we expect several participants to stop using the intervention. We also expect participants to drop out of the study, i.e., to fail to take part in the follow-up assessments. Fourth, the primary aim of guidance in this study is to support participants to adhere to the intervention schedule. However, it may be the case that the level of support may be too low to have a meaningful incremental impact on the guided intervention in terms of psychopathological outcomes and cost-effectiveness compared to the unguided intervention. Fifth, due to limitations with regard to feasibility, only self-reported measurements will be used. Sixth, even though most of the self-rated measures show good psychometric properties, only a few have been validated in the context of online-assessments, for example the TLFB [55]. Seventh, in this trial, we will use a waiting list control group. This may increase the risk of overestimating intervention effects compared to an assessment-only control group [28]. However, due to practical and ethical reasons, we decided to give all control participants access to the unguided intervention after they will have finished the follow-up assessment.

## Conclusions

This study allows us to assess the (cost-)effectiveness of a web-based intervention for reducing alcohol consumption in a heterogeneous workforce. If shown effective, the CWT intervention would be a flexible solution for employees who do not use traditional services for alcohol treatment and for companies and society to overcome the high risk of ill-health and productivity losses due to alcohol-related problems. If the intervention works as intended, the next step would be to investigate which guidance format is the most feasible for dissemination to a broad community.

## Abbreviations

AUD: Alcohol use disorder
PNF: Personalized normative feedback
CWT: Clever weniger trinken (name of the intervention)
RCT: Randomized controlled trial
WLC: Waiting list control group
AUDIT: Alcohol use disorders identification test
BDI: Beck depression inventory
HAPA: Health action process approach
PST: Problem solving therapy
ART: Affect regulation training
TLFB: Timeline follow back
APQ: Alcohol problems questionnaire
RTCQ: Readiness to change questionnaire
DASS-21: Depression anxiety stress scale (short form)
IS: Irritation scale
ERI-SF: Effort reward imbalance questionnaire (short form)
WLQ-8: Work limitations questionnaire
GSE: General self-efficacy scale
ATSPPHS-SF: Attitudes toward seeking professional psychological help scale (short form)
INEP: Negative-effects of psychotherapy inventory
CSQ-8: Client satisfaction questionnaire
AQoL-8D: Assessment of quality of life
TiC–P-G: Trimbos and institute of medical technology assessment cost questionnaire for psychiatry
PPA: Per protocol analyses
CONSORT: Consolidated standards of reporting trials
NNT: Number needed to treat
ICER: Incremental cost-effectiveness ratio
QALYs: Quality-adjusted life years
